#### Statistical Methods for Primary and Secondary Outcomes

Analyses are to be conducted after drug administration to all patients has been completed and the data have been finalized. For all efficacy assessments, the full analysis set analysis will be set as the primary analysis, and the per protocol set analysis will be conducted as a reference. A safety analysis will also be conducted using the safety analysis set.

The distribution of research subject background data and the summary statistics in each analysis set will be calculated for each group. For nominal variables, category frequency and percentage will be shown for each group. For continuous variables, the summary statistics (ie, number of cases, average value, standard deviation, minimum value, median value, and maximum value) will be calculated for each group.

Intergroup comparisons will be performed with the Pearson Chi-squared test or Fisher exact test for nominal variables. The 2-tailed Student *t* test or Wilcoxon signed-rank test will be used for continuous variables. The significance level will be set at 10% for both sides.

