### Trial Design

This is an investigator-initiated, exploratory, prospective, multicenter, parallel-group, open-label, randomized controlled trial. Figure 1 describes and outlines the design in more detail. The first trial participant was enrolled on April 3, 2020. Recruitment is expected to be completed on September 30, 2020, while the follow-up of all participants is expected to be completed by October 31, 2020.

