### Patient Registration and Allocation Method

After obtaining written consent from the research participants, the principal physician or subphysician will confirm whether a research participant is suitable for the trial by verifying the inclusion and exclusion criteria, promptly performing electronic data capture (EDC)-based patient registration, and acquiring the allocation results.

A stratified block randomization method will be used to allocate participants into 2 groups, the ciclesonide group and symptomatic treatment group. Allocation adjustment factors include the numbers allocated to each facility, fever temperature (ie, over or below 37.5°C), and age (ie, over or under 60 years). Allocation results will be displayed on the EDC system after inputting and confirming the allocation adjustment factors into the EDC system.

The principal physician or subphysician will commence research treatment in accordance with the allocation results. Research participants will be issued a research ID that is specific to the proposed research.

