### Statistical Methods

#### Sample Size

The sample size for the RACCO trial will be 90 patients (ie, n=45 for the ciclesonide group and n=45 patients for the symptomatic treatment group) to control for pneumonia onset and allow for the full analysis of study participants to complete the study.

Based on our experience, 35% of patients who have tested positive for COVID-19 without pneumonia symptoms will have pneumonia during the follow-up period. The necessary number of cases for a 2-sided α-level of 10% and power of 80% for cases with incidence percentages of 30%, 35%, 40%, and 50% in the standard treatment group and incidence percentages of 5%, 10%, 15%, and 20% in the trial treatment group are shown in Figure 3.

The effect of controlling the pneumonia onset percentage to 25% would mean that the drug is clinically effective. The numbers highlighted in grey in Figure 3 are the sample sizes necessary for detecting effects with a power of 80% in cases where a 25% pneumonia onset control is present. For example, if the pneumonia onset percentage of the standard treatment and trial treatment groups were hypothetically set to 35% and 10%, respectively, the required sample size would be 84. Factoring in cases where consent may be withdrawn during the trial or participants drop out, the target number of cases for the present research will be set at N=90. The target number of cases will be specified for each implementing medical institution.

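### The nonparametric test named for comparing the two arms is a paired test (Wilcoxon signed-rank), which does not apply to independent randomised groups

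*Protocol article*

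**What the plan says.** The testing paragraph under Statistical Methods for Primary and Secondary Outcomes begins with the comparison of the two arms: "Intergroup comparisons will be performed with the Pearson Chi-squared test or Fisher exact test for nominal variables". The next sentence offers, for continuous data, a two-tailed Student t test or the signed-rank test: "Wilcoxon signed-rank test will be used for continuous variables". One significance level closes the paragraph and covers both sentences: "The significance level will be set at 10% for both sides".

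The design is set out under Trial Design: "This is an investigator-initiated, exploratory, prospective, multicenter, parallel-group, open-label, randomized controlled trial". Under Patient Registration and Allocation Method the article adds: "A stratified block randomization method will be used to allocate participants into 2 groups". It describes no matched pairs and no crossover. The rank-sum (Mann-Whitney) test is not named anywhere.

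**The concern.** The signed-rank test is a one-sample test on differences within pairs. Two independently randomised arms supply no such differences. An analyst who follows the sentence literally has three courses, and none gives a sound comparison of treatments:

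- With unequal arms, the test cannot be run between groups at all.
- With equal arms, it can be run only after pairing patients arbitrarily, for example by row order, and the p value then depends on that order.
- Run within each arm, it tests change over time and not the difference between treatments. In a self-limiting illness, change over time would be expected in both arms.

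An analyst who silently substitutes the correct test departs from the published plan. In a small open-label trial, that invites questions about when the test was chosen.

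**Working it through.** **1. Is a paired reading possible?** The sentence on continuous variables does not repeat that the comparison is between groups, but it stands between the sentence that does and the shared significance level. The article plans no before-after test within an arm. Where change from day 1 is analysed (vital signs, symptom scores, inspection findings, peak flow), the arms are compared through mixed models for repeated measures. The signed-rank test is therefore meant as a between-group test.

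**2. Are there pairs?** No. Patients are randomised individually in stratified blocks. Blocks and strata balance the arms but do not create matched pairs.

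**3. Will the analysed arms be equal?** The plan is "n=45 for the ciclesonide group and n=45 patients for the symptomatic treatment group", but equality at analysis is unlikely:

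- Sample Size allows for withdrawal and dropout.
- Analysis Sets removes patients without a baseline CT and those with serious violations. The per protocol set also drops patients below 90% compliance; if that means the trial drug, it can remove patients from the ciclesonide arm only.
- Methods for Handling Missing Data rules out filling in missing values.
- Randomisation adjusts for facility, fever (2 levels) and age (2 levels). With 21 hospitals (Abstract) or 22 (Study Setting), full crossing gives 21 × 2 × 2 = 84 or 22 × 2 × 2 = 88 cells for 90 patients. Many blocks would be incomplete.

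With 45 and 43 observations, the signed-rank routine stopped with an error, as expected.

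**4. What happens if the arms are equal and pairs are made up?** This was simulated at 45 per arm, two-sided 10% level, 5,000 runs. The data are assumed, not taken from the article.

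| Data | True shift (SD) | Rank-sum, share rejected | Signed-rank on arbitrary pairs, share rejected |
|---|---|---|---|
| Normal | 0 | 0.095 | 0.092 |
| Normal | 0.5 | 0.744 | 0.738 |
| Lognormal | 0 | 0.105 | 0.103 |
| Lognormal | 0.5 (log scale) | 0.756 | 0.704 |

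The type I error stays near 10%. Power is almost unchanged with normal data and about 5 points lower with lognormal data (0.756 − 0.704 = 0.052).

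The larger fault is that the result is not unique. One simulated dataset of 45 v 45 gave a single rank-sum p value of 0.226. Over 2,000 random pairings of the same data, the signed-rank p value had median 0.318, central 95% range 0.160 to 0.502, and extremes 0.067 and 0.599. Most pairings fell on the same side of 10%, but some crossed it.

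**5. Is the sample size affected?** No. The basis is "The necessary number of cases for a 2-sided α-level of 10% and power of 80"%, and the worked example is "treatment groups were hypothetically set to 35% and 10%, respectively, the required sample size would be 84". With p1 = 0.35, p2 = 0.10, mean 0.225, z = 1.645 and 0.842:

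- Uncorrected n per arm = [1.645·√(2·0.225·0.775) + 0.842·√(0.35·0.65 + 0.10·0.90)]² / 0.25² = (0.971 + 0.474)² / 0.0625 ≈ 33.4, rounded up to 34.
- With continuity correction: (n/4)·[1 + √(1 + 4/(n·0.25))]² = (34/4)·[1 + √1.4706]² ≈ 41.6, rounded up to 42.
- Total 2 × 42 = 84, as stated.

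This rests on the binary primary endpoint and does not use the Wilcoxon test.

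**The case against.** The strongest reply concerns reach. Most endpoints have their own test: Fisher exact for the primary endpoint, mixed models for the repeated measures, and t tests for fever duration and oxygen therapy duration. No endpoint section names a Wilcoxon test. The general rule follows directly on the background-data summaries and uses 10%, whereas the secondary and safety sections use 5%, so it may be meant mainly for baseline tables. The same sentence also names a valid test, the Student t test, and does not say when the Wilcoxon test would replace it. Finally, the article has other apparent translation slips, such as least mean square where a least-squares mean seems meant, and an analyst would notice the problem at once.

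Much of this stands. The reach is narrow, the cause is probably a naming slip, and the simulation shows no inflation of type I error. It does not remove the fault. The section heading covers primary and secondary outcomes. The section on virus genomes promises between-group comparison of genome and antibody quantities without naming a test, so the general rule is the only stated source, although the average difference reported there points towards a mean-based method. Nor is this a detail left to a statistical analysis plan: the article names a specific test, and it is the wrong one.

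**Conclusion.** The concern holds. As written, the nonparametric rule for between-group comparison names a test that does not apply to this design: it cannot be computed with unequal arms, and with equal arms its p value depends on an arbitrary pairing.

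It affects any continuous comparison under the general rule for which the Wilcoxon option is chosen. That covers background data and plausibly the viral genome and antibody quantities. The primary analysis, the sample size and the endpoints with their own named tests are not affected. It should be corrected, but it does not threaten the trial's main conclusion.

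The conclusion rests on reading the sentence as a between-group rule, for which the context leaves no real alternative. The simulated p values and rejection rates rest on assumed data and serve only as illustration.

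**What to change.** In Statistical Methods for Primary and Secondary Outcomes, replace the signed-rank test with the Wilcoxon rank-sum (Mann-Whitney) test. Check the statistical analysis plan, which was not available here, for the same wording. A Hodges-Lehmann shift estimate with its confidence interval would be a useful companion to the p value, but it is optional.

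The required correction is one term. It changes no sample size, endpoint or data collection.

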#### Secondary Endpoint Analysis

A secondary endpoint analysis will be conducted with the aim of supplementing the primary analysis results. The significance level of hypothesis testing will be set at 5% for both sides, and the 95% confidence interval for both sides will be calculated.

##### Pneumonia Exacerbation

The number and percentage of cases divided among 3 assessment levels, including remission or stabilization cases, potential exacerbation cases, and clear exacerbation cases, will be calculated, and intergroup comparisons will be conducted using the Mantel test.

##### Change in the Quantity of the Virus Genomes

Quantified virus genomes at each assessment time point, quantified antibody values, and related changes will be calculated for each group and illustrated over time. Furthermore, the average difference between groups and the 95% confidence intervals will be calculated, and intergroup comparisons will be conducted.

##### Body Temperature, Respiratory Rate, Oxygen Saturation, Systolic Blood Pressure, and Pulse Rate

The recorded metrics of each assessment criterion at each assessment time point will be calculated for each group, and changes over time will be illustrated. The least mean square and 95% confidence interval at each assessment time point, as well as the least mean square difference and 95% confidence interval, will be calculated. The amount of change from day 1 will be used as the result variable by using mixed models for repeated measures (MMRMs), and intergroup comparisons will be conducted.

##### Fever Duration

The recorded fever temperature for the number of days in which a fever of at least 37.5°C was present during the trial period will be calculated, and intergroup comparisons will be conducted using a 2-tailed *t* test.

##### Symptom Changes

Recorded symptom scores (ie, malaise/appetite scores) at each time point will be calculated, and changes over time will be illustrated. The least mean square and 95% confidence interval at each assessment time point, as well as the least mean square difference and 95% confidence interval, will be calculated. The amount of change from day 1 will be used as the result variable by using MMRMs, and intergroup comparisons will be conducted.

##### Changes in Inspection Findings

Recorded metrics for the continuous values obtained through clinical inspection will be calculated at each time point. Furthermore, the least mean square and 95% confidence interval at each assessment time point, as well as the least mean square difference and 95% confidence interval, will be calculated. The amount of change from day 1 will be used as the result variable by using MMRMs, and intergroup comparisons will be conducted.

For categorical variables obtained from inspection findings, the number and percentage of each criterion at each time point will be calculated, and intergroup comparisons will be conducted using a Mantel test.

##### Oxygen Therapy

The number and percentage of research participants who underwent oxygen therapy during the trial period will be calculated for each group and compared using the Fisher exact test. Furthermore, the average oxygen therapy duration and its 95% confidence interval will be calculated for each group, and intergroup comparisons will be conducted using a 2-tailed *t* test.

##### Hospital Discharge

The number and percentage of research participants who are discharged from the hospital will be calculated for each group, and comparisons will be performed using the Fisher exact test. Furthermore, a Kaplan-Meier curve for the time until hospital discharge will be calculated.

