### Provisions of Posttrial Care

The expected research participation period will last for approximately 1 month, after consent acquisition (ie, 1 week for the protocol treatment period and 3 weeks for the follow-up period). Research participants will be hospitalized during the treatment period, and outpatient follow-up observations will be permitted following the end of the protocol treatment period. In cases where the research participants experience adverse events linked to the treatment, follow-up examinations are to be conducted until the principal physician or subphysician has ensured the safety of the research subject.

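### The only named comparison for hospital discharge is a Fisher test on the proportion discharged, which is likely to have little power in this population; a log-rank test of time to discharge would use the data better

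*Protocol article*

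**What the plan says.** The Hospital Discharge paragraph of the protocol article first calls for a count and percentage of discharged patients in each arm. It then states: "comparisons will be performed using the Fisher exact test. Furthermore, a Kaplan-Meier curve for the time until hospital discharge will be calculated". The comparison is thus fixed on a proportion, and timing receives only a curve. The paragraph names no test or effect estimate for that curve, and it does not say at which day the proportion is taken.

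The Secondary Endpoint Analysis section sets the error level for this family of analyses: "The significance level of hypothesis testing will be set at 5% for both sides". The Sample Size section gives "n=45 for the ciclesonide group and n=45 patients for the symptomatic treatment group". Provisions of Posttrial Care describes participation of about a month, split as "1 week for the protocol treatment period and 3 weeks for the follow-up period", with patients in hospital during treatment and outpatient observation allowed afterwards.

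The Oxygen Therapy paragraph, just before Hospital Discharge, handles a similar outcome differently. It tests the proportion treated with Fisher and also tests the duration, with a t test.

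**The concern.** A proportion discharged carries information only while a fair number of patients are still in hospital. Several features of the protocol suggest that few will be by the end of follow-up. Disease is asymptomatic or mild at entry, with no clear pneumonia on simple chest images. The required stay is the treatment week. Later visits are planned as outpatient visits, and Table 1 sets rules for patients already discharged at days 15, 22 and 29.

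If most patients in both arms have left by about day 29, a treatment that shortens the stay changes when they leave and hardly changes how many have left. The named test would then probably be non-significant and would stand beside a curve with no named comparison. Any test chosen after looking at that curve would be post hoc.

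**Working it through.** **1. The plan's own figure.** No power or sample size is stated for discharge. The stated figure is for the primary endpoint: "were hypothetically set to 35% and 10%, respectively, the required sample size would be 84", at two-sided 10% and 80% power.

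- Uncorrected, per arm: n' = [1.645·√(2·0.225·0.775) + 0.842·√(0.35·0.65 + 0.10·0.90)]² / 0.25² = 33.4, rounded up to 34 (68 in total).
- With continuity correction: n = (n'/4)·[1 + √(1 + 4/(n'·0.25))]² = 41.05, rounded up to 42 (84 in total).

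The stated 84 is reproduced with the continuity correction. It concerns pneumonia only and says nothing about discharge.

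**2. Inputs for discharge.**

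- From the documents: 45 per arm; two-sided 5%; follow-up to about day 29.
- Assumed, because the documents give neither: the control proportion discharged by the end of follow-up, p (50% to 98%), and the discharge hazard ratio, HR (1.5 to 2.0).
- Also assumed: proportional discharge hazards, complete follow-up, and the proportion taken at the end of follow-up.

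**3. Formulas.**

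- Proportion discharged on ciclesonide: q = 1 − (1 − p)^HR.
- Fisher power: sum of the binomial probabilities of all pairs of counts (45 per arm, p and q) with two-sided Fisher p ≤ 0.05.
- Log-rank power (Schoenfeld): Φ(√(d/4)·ln HR − 1.96), with d = 45·(p + q) discharges.

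Example with p = 0.90 and HR = 1.8: q = 1 − 0.10^1.8 = 0.984. Then d = 45·(0.90 + 0.984) = 84.8, √(84.8/4)·0.588 − 1.96 = 0.75, and Φ(0.75) is about 77%.

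**4. Results at HR 1.8.**

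| Control discharged (assumed) | Ciclesonide discharged | Fisher power | Log-rank power |
|---|---|---|---|
| 50% | 71.3% | 46% | 58% |
| 70% | 88.6% | 49% | 70% |
| 80% | 94.5% | 44% | 74% |
| 90% | 98.4% | 17% | 77% |
| 95% | 99.5% | 2% | 79% |
| 98% | 99.9% | about 0% | 79% |

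**5. Sensitivity to the hazard ratio, at 90% discharged.** HR 1.5: Fisher 10%, log-rank 46%. HR 2.0: Fisher 21%, log-rank 89%.

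**6. What Fisher would need.** If all 45 are discharged in one arm, 40 of 45 in the other gives p = 0.056 and 39 of 45 gives p = 0.026. So at least six patients in one arm, and none in the other, would have to be still undischarged.

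**The case against.** The strongest objection is that saturation is not in the document. A reader might infer that discharge will be near 100% in both arms by day 29, so that the Fisher test cannot separate them. The article gives no discharge rate and no time point for the proportion; day 29 is only the end of follow-up. It also provides for patients who are still inpatients late on. Several day 22 and day 29 assessments are waived only for those already discharged, and the Sample Size section expects pneumonia in 35% of patients. This objection stands. Saturation is an inference from the population and the visit schedule, and the size of the loss depends on it: at 50% discharged the gap is 46% against 58%.

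Second, the analysis plan is not shown and may name a test for the Kaplan-Meier curve. This also stands as far as it goes: silence on a test does not mean that timing will never be compared. The point therefore rests on what the article does fix, which is Fisher on the proportion as the named comparison. The Oxygen Therapy paragraph shows that, where the authors wanted a test of duration, the article named one.

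Third, a shift in timing would be visible on the planned curve, so it goes too far to say that a shorter stay would necessarily be reported as no difference. That is correct. The narrower statement holds: the named test would probably miss the shift.

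Fourth, discharge is one of many analyses meant to supplement the primary result in an exploratory trial, and its timing is open to influence because the trial is open-label. This limits the importance of the point but does not favour the proportion over the time.

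**Conclusion.** The point holds in a conditional form and is minor. The article makes a Fisher test on the proportion discharged the only named comparison and leaves time to discharge with a curve. Log-rank power is higher than Fisher power at every control discharge rate examined, from 50% to 98%. At 90% to 98% discharged, which is likely but assumed, and an assumed hazard ratio of 1.8, it is 77% to 79% against about 17% falling to about 0%. At 50% to 80% the comparison is 58% to 74% against 44% to 49%.

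These figures rest on proportional discharge hazards, complete follow-up and 45 per arm. The document does not support the claim that the proportion will be near 100%, nor that a shortening of stay is bound to go unreported. A log-rank test would not make discharge a well-powered endpoint either: at a hazard ratio of 1.5 and 90% discharged, its power is 46%. No primary conclusion is affected.

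**What to change.** In the Hospital Discharge paragraph, make a two-sided 5% log-rank test of time to discharge the between-group comparison. Report the median time in each arm and a discharge hazard ratio with 95% CI. Keep any participant who dies in the risk set, as not discharged, to day 29, so that a death is not treated as if discharge could still have followed. Report the number and percentage discharged descriptively, with the day stated.

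The cost is one analysis line. The discharge times are already needed for the planned curve, and the sample size does not change. The downside is that knowledge of the arm can influence discharge timing in an open-label trial. The planned curve has the same weakness, and the report should say so.
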